## Analyses

Multiple linear regression will be used to investigate the associations of the main predictor variable, change in RT3 VM counts/hour/week (ΔRT3) from baseline to 3 months, with the main outcome variable change in functional outcome (ΔRMDQ). The change score will be calculated by subtracting each participant's 3 month RMDQ score from their baseline RMDQ score. Unadjusted and adjusted analyses will be performed. Adjusted analyses will include the following variables, shown to be putatively associated with both PA and functional recovery in LBP: age, gender, occupation, baseline pain level (pain questionnaire), functional status (baseline RMDQ) and baseline measurements of depression, anxiety, emotional distress and fear avoidance (GHQ12 and FABQ). We plan to analyze each of the explanatory variables univariately initially to assess the relationship with the dependant variable (RMDQ change). We will include factors in the model which in univariate analyses have a *p*-value < 0.10. The significant explanatory variables contained in the separate models will then be combined and re-examined using further modeling. We plan to use multiple linear regression to assess which of the included explanatory variables and/or their interactions with PA change predict change in RMDQ. For those variables which remain in the final model, an examination of their significance (p < 0.05) will be undertaken to evaluate their contribution to the final model.

At 1 year the relationship between ΔRT3 and presence or absence of on-going low back pain (Y/N) from the modified Nordic LBP questionnaire will be investigated using logistic regression. At 1 year the relationship between the BPAQ change score from baseline (pre-LBP) to BPAQ score at 1 year (ΔBPAQ) with the outcome of on-going LBP (Y/N) will also be explored using logistic regression.

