### Hypotheses

Three specific hypotheses will be tested:

1. Positive changes in PA levels of participants with acute LBP (from baseline to 3 months) are a positive predictor of recovery (defined from change score in *Roland Morris Disability Questionnaire*) [54] at 3 months and at 1 year;

2. Psychosocial factors including levels of fear avoidance beliefs, depression and anxiety and occupational factors including types of occupation and levels of manual or sedentary work act as confounders in the relationship between activity change and the course of LBP over a 1 year period;

3. Restoration of "normal" levels of PA at baseline and at 3 months is a positive predictor of functional recovery over a 1 year period.

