### Inclusion and exclusion criteria

To be eligible to take part in the study, participants must fulfil the following criteria:

1) Have an episode of LBP of 6 weeks or less, proceeded by at least 3 months of relative freedom from symptoms. These inclusion criteria will effectively exclude the chronic LBP population (defined as symptoms exceeding 3 months) [55].

2) Be between the ages of 18 and 65 years (working age population).

3) Be English speaking and able to provide informed consent to PA monitoring and follow up for 12 weeks.

4) Have no other pre-existing conditions which limit their mobility of PA levels.

5) Be receiving physiotherapy treatment for this current episode of acute LBP. This threshold was chosen to make results generalizable to this specific patient population.

6) Have a minimal score of 4 on the RMDQ. This score will allow for the detection of the smallest clinically important change [55].

The following exclusion criteria will be investigated at an initial screening interview by the PI prior to recruitment:

1) Serious or systemic spinal pathologies including persistent or progressive neurological deficit, intractable pain, spinal surgery, or inflammatory disorders as assessed by their health practitioner or by screening questions from the co-investigator.

2) Any history of current or past medical problems (other than LBP) which prevent participants from undertaking usual day-to-day activities.

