### Sample size and statistical power

We calculated sample size based upon the detection of a difference in change in RMDQ from baseline to three months in two groups classified as high changers in PA and low changers, as defined by the upper quartile of change in PA. This is a simplification of the actual analysis, but is conservative. The sample size is calculated for 80% power at a two-sided type I error rate of 0.05. Assuming a standard deviation of change in RMDQ score of 5.4 over a 3 month period, [78,79] the detection of a clinically meaningful change of 4 points in the RMDQ score from week 1 to week 12 [55,80], and an assumption of unequal group sizes, the required sample size is 65 participants. Previous research employing the RT3 in free living has found loss of data due to technical issues including monitor malfunction to be a significant issue [81,82]. Therefore a reasonably high attrition rate and potential dropout rate of 40-50% will be used over the 3 time points and this requires data from approximately 120 participants to be collected (Figure 1).

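### Screening each factor alone against RMDQ change, without baseline RMDQ in the model, mixes baseline severity with recovery and can hide a real adverse factor before it reaches the adjusted model

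*Protocol article*

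**What the plan says.** All of the following is in the protocol article.

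- **Outcome** (Analyses): "The change score will be calculated by subtracting each participant's 3 month RMDQ score from their baseline RMDQ score". A positive value is improvement. The Hypotheses section also ties recovery to this score: positive activity changes "are a positive predictor of recovery (defined from change score in" the RMDQ.
- **Unadjusted step** (Analyses): "Unadjusted and adjusted analyses will be performed".
- **Screen** (Analyses): "We plan to analyze each of the explanatory variables univariately initially to assess the relationship with the dependant variable (RMDQ change"). Then: "We will include factors in the model which in univariate analyses have a" p-value below 0.10. Factors that pass are combined in further models, and those remaining at the end are examined at p < 0.05.
- **Candidates** (Analyses): age, gender, occupation, baseline pain, "functional status (baseline RMDQ) and baseline measurements of depression, anxiety, emotional distress and fear avoidance (GHQ12 and FABQ").
- **Entry rule** (Inclusion and exclusion criteria): "Have a minimal score of 4 on the RMDQ".

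The adjusted analyses list baseline RMDQ. The screening and unadjusted models make no provision for it. The text also does not settle whether the listed variables enter regardless or only after passing the screen.

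**The concern.** Baseline RMDQ is one of the two parts of the outcome. People who start worse have more room to improve, and part of a high first score is transient, so baseline RMDQ will usually correlate positively with the change score whether or not severity affects the course of the episode. Any factor correlated with baseline RMDQ inherits a share of that correlation, in the direction of more of the factor going with more improvement.

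This distorts the screen in two ways. A factor unrelated to 3-month function once baseline is known is admitted too often. A factor that slows recovery has its negative slope partly or wholly cancelled, fails p < 0.10 and is dropped. The second is worse, because a dropped factor never reaches the model in which baseline RMDQ would have put it right. Objective 2 and Hypothesis 2 ask whether psychosocial and other baseline factors confound or modify the relation between activity change and outcome. The factors most at risk of being lost at the screen are among those named there.

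**Working it through.** **Inputs from the document** (Sample size and statistical power): SD of RMDQ change 5.4; n = 65 required, about 120 recruited. The plan gives no figure of its own on this point, so there is none to reproduce.

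**Assumptions, because the document gives no values:** baseline SD σB and 3-month SD σF each between 4 and 6, central 5; correlation r = 0.3 between a factor Z and baseline RMDQ; for an adverse factor, partial correlation π = 0.3 with worse 3-month RMDQ given baseline.

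**Step 1. Correlation of baseline B with Δ = B − F.** Since Var(Δ) = σB² + σF² − 2ρσBσF = 5.4² = 29.16,

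- ρ = (σB² + σF² − 29.16) / (2σBσF)
- corr(B, Δ) = (σB² − σF² + 29.16) / (2 × 5.4 × σB)

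At σB = σF = 5: ρ = 20.84/50 = 0.417 and corr(B, Δ) = 29.16/54 = 0.54.

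**Step 2. Correlation of Z with Δ.**

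- Null factor (π = 0): r × corr(B, Δ) = 0.3 × 0.54 = 0.162.
- Adverse factor: 0.162 − π√(1 − r²) × σF√(1 − ρ²)/5.4 = 0.162 − 0.3 × 0.954 × (5 × 0.909)/5.4 = 0.162 − 0.241 = −0.079.

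About two thirds of the adverse signal is cancelled (0.162/0.241 = 0.67).

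**Step 3. Chance of passing two-sided p < 0.10 at n = 65** (Fisher z, standard error 1/√62).

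- Null: 0.1634 × 7.874 = 1.287; P(Z > 1.645 − 1.287) = 0.36.
- Adverse: 0.0792 × 7.874 = 0.623; P(Z > 1.022) + P(Z < −2.268) = 0.153 + 0.012 = 0.165.
- Adverse with baseline RMDQ in the model: atanh(0.3) × √61 = 2.417; P(Z > −0.772) = 0.78.

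**Step 4. Simulation** (bivariate normal scores, 20,000 studies per setting, n = 65, r = 0.3). The last column is baseline RMDQ tested alone.

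| σB / σF | corr(B, Δ) | Null factor passes | Adverse factor passes | Baseline RMDQ passes p < 0.10 |
|---|---|---|---|---|
| 4 / 4 | 0.68 | 49% | 10% | 100% |
| 4 / 5 | 0.47 | 30% | 23% | 99% |
| 4 / 6 | 0.21 | 14% | 54% | 52% |
| 5 / 4 | 0.71 | 52% | 10% | 100% |
| 5 / 5 | 0.54 | 37% | 17% | 100% |
| 5 / 6 | 0.34 | 21% | 39% | 87% |
| 6 / 4 | 0.76 | 58% | 12% | 100% |
| 6 / 5 | 0.62 | 44% | 12% | 100% |
| 6 / 6 | 0.45 | 28% | 25% | 99% |

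With baseline RMDQ in the model, the null factor passes in about 10% and the adverse factor in 78–79% in every row. At n = 120 and SDs of 5, the null factor passes in 55%, and the adverse factor in about 22% against 96%.

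**Step 5. Bounded scores.** With integer scores from 0 to 24, entry at 4 or more and assumed means of 11 and 5, the null factor passes in 34%, and the adverse factor in 17% against 78%. The normal model is not driving the result.

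**Step 6. Entry rule.** Selecting on baseline leaves the slope of Δ on B unchanged: at SDs of 5 it is 1 − ρ = 0.58 before and after truncation. The correlation falls, from 0.54 to 0.44 with an assumed baseline mean of 8, or to 0.47 with a mean of 10.

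**The case against.** **The adjusted model lists baseline RMDQ.** This stands. With it in the model, regressing change or 3-month RMDQ gives the same factor coefficient apart from sign, so adjusted coefficients do not carry this fault. A null factor wrongly admitted is then mostly a surplus covariate. It does not help a real factor lost at the screen. Nor is retention of baseline RMDQ assured if it too must pass the screen: with SDs of 4 and 6 it passes in only about half of studies.

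**Recovery is defined by the change score, and the objectives ask about confounding.** This also stands in part. Under that definition, a group that starts worse and improves more really does change more. The crude slopes mix two things and answer a different question; a reader might infer that they are simply wrong, or that the trial would announce false predictors of recovery. The document does not support that, because it uses the univariate step to choose factors and draws conclusions from the final model.

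**Three stronger readings fail.**

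- A reader might infer that the entry rule of RMDQ 4 or more aggravates the slope problem. Selection on baseline leaves the slope alone and weakens the correlation.
- A reader might infer that baseline RMDQ will be significant whatever the truth. That depends on the two SDs: at 4 and 6 it reaches p < 0.05 in about 40% of studies.
- A reader might infer that the unadjusted ΔRT3 estimate is biased to a similar degree. It is affected only as far as ΔRT3 correlates with baseline RMDQ, which the document does not quantify.

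**Forcing in all listed covariates would cure the masking.** True, and this overlaps with the general case against p-value screening. The crude tables and the reading of baseline RMDQ's own p-value would still need relabelling.

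**Conclusion.** The point holds for the screening and unadjusted models. As planned, the p < 0.10 screen tests a mixture of baseline coupling and association with recovery for any factor correlated with baseline RMDQ. In the central case a genuinely adverse factor passes in about 17% of studies instead of 79%, and a factor with no effect given baseline passes in about 37% instead of 10%. Across SDs of 4 to 6 the figures are about 10–54% and 14–58%. They rest on assumed SDs, an assumed factor-baseline correlation of 0.3 and an assumed partial correlation of 0.3; only the change SD of 5.4 and the sample sizes come from the plan. The distortion shrinks as the 3-month SD grows relative to baseline, and vanishes only when σF = σB/ρ.

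The consequence is loss of real confounders at the screen and crude results open to misreading. Adjusted coefficients are not affected when baseline RMDQ is retained. The change should be made, but the main adjusted analysis is not invalid.

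**What to change.** - Force baseline RMDQ into every 3-month model, whatever its p-value. This includes each screening model and a baseline-adjusted ΔRT3 model. Either ΔRMDQ or 3-month RMDQ may be the outcome, since the factor coefficient is the same apart from sign.
- State that screening decisions, if screening is kept, use these baseline-adjusted p-values.
- Keep the crude univariate and crude ΔRT3 results if wanted, labelled descriptive.
- Do not read the p-value of baseline RMDQ against ΔRMDQ, alone or in the final model, as evidence that functional status predicts recovery. It tests whether the slope of 3-month on baseline RMDQ equals 1.

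The cost is wording and one degree of freedom per model. Baseline RMDQ is already collected, because it is needed for eligibility and for the change score. The crude estimates lose their inferential role.

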**Discussion:**

This research will investigate levels and changes in activity levels of an acute LBP cohort and the predictive relationship to LBP recovery. The results will assess whether occupational, psychological and behavioural factors affect the relationship between free living PA and LBP recovery. Results from this research will help to determine the strength of evidence supporting international guidelines that recommend restoration of normal activity in managing LBP.

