## Methods

### Research objectives

1. To investigate the predictive relationship between change in objectively measured PA levels in a cohort of patients with acute (< 6 weeks' duration) LBP [54] from baseline to 3 months, and change in functional outcome at 3 months and recovery over a 1 year period.

2. To assess the effect of occupation and occupational activity levels, personal factors, pain levels, functional status and psychosocial profile on the relationship between PA levels and LBP outcomes at 3 months and at 1 year.

3. To determine the relationship between restoration of "normal" levels of PA as considered by the patient and functional recovery.

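### Read literally, the p<0.10 univariate screen decides which interactions with PA change are ever tested, which serves the effect-modification part of Objective 2 poorly and conflicts with the fixed adjustment list

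*Protocol article*

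**What the plan says.** All of this is in the protocol article.

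- **Research objectives**, second item: "To assess the effect of occupation and occupational activity levels, personal factors, pain levels, functional status and psychosocial profile on the relationship" of PA with outcome, at both follow-up times.
- **Abstract, Discussion**: "The results will assess whether occupational, psychological and behavioural factors affect the relationship between free living PA and LBP recovery".
- **Hypotheses**, item 2, describes the psychosocial and occupational factors as confounders. **Research protocol and timetable** does the same when it introduces the occupational data and the other measures.
- **Analyses** begins with an unconditional adjustment list: age, gender, occupation, baseline pain, baseline RMDQ, GHQ12 and FABQ.
- **Analyses** then sets out a sequence. The first step is "We plan to analyze each of the explanatory variables univariately initially to assess the relationship with the dependant variable (RMDQ change"). The entry rule is "We will include factors in the model which in univariate analyses have a *p*-value < 0.10". Next, "The significant explanatory variables contained in the separate models will then be combined and re-examined using further modeling". Multiple regression is then used to assess "which of the included explanatory variables and/or their interactions with PA change predict change in RMDQ". Last, for variables that remain, "an examination of their significance (p < 0.05) will be undertaken to evaluate their contribution to the final model".

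No other route to an interaction test is described.

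**The concern.** Whether a factor is associated with average ΔRMDQ and whether it changes the slope of ΔRMDQ on ΔRT3 are different questions. The screen answers the first and is used to decide whether the second is asked. Suppose manual and sedentary workers recover equally on average, but recovery tracks PA change closely in one group and hardly at all in the other. Occupation type would then usually fail the screen and its interaction would not be fitted.

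At stake is the part of Objective 2 and of the abstract that asks whether factors affect the PA-recovery relationship, over and above the confounding question in Hypothesis 2. If the final model holds no interaction for a factor, the reader cannot tell whether the term was fitted and found small or never fitted.

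**Working it through.** The protocol gives no figure for the performance of this procedure, so there is none to reproduce. The check takes its rules and sample size and asks how often a true modifier reaches the interaction test.

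**Inputs from the protocol.** Screen at p<0.10 and final level 0.05 (Analyses); n = 65 analysable and SD of ΔRMDQ 5.4 (Sample size and statistical power).

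**Assumptions, not in the protocol.** A 50:50 binary factor m = ±0.5, independent of ΔRT3. ΔRT3 in SD units, z ~ N(μ, 1), with μ = 0, 0.5 or 1. Model y = 1.5z + d·z·m + e, with e ~ N(0, 5²), where d is the difference in slopes in RMDQ points per SD. At d = 3 the SD of y is √(25 + 1.5² + 3²/4) = 5.43, close to the protocol's 5.4.

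**Step 1: power of the interaction test with no screen.** The variance of z·m about its group means is 0.25, so SE(d) ≈ 5/√(65 × 0.25) = 1.24.
- d = 1.5: ratio 1.21, approximate power Φ(1.21 − 1.96) = 23%
- d = 2: ratio 1.61, 36%
- d = 3: ratio 2.42, 68%
- d = 4.7: ratio 3.79, 97%

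Simulation (4,000 runs per cell, t-tests) gives slightly less: about 20%, 33%, 62% and 94%.

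**Step 2: chance of passing the screen.** The marginal group difference is d·μ, with SE ≈ 2·SD(y)/√65.
- μ = 0: the difference is 0, so the pass rate is 10% by definition, whatever d is.
- μ = 0.5, d = 3: 1.5/1.35 = 1.11, pass rate 30%. With d = 4.7: 2.35/1.42 = 1.65, pass rate 50%.
- μ = 1, d = 3: 3/1.35 = 2.23, pass rate 72%. With d = 4.7: 4.7/1.42 = 3.31, pass rate 95%.

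**Step 3: both steps together (simulation, n = 65).**

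| Slope difference d | Always tested | Screened, μ = 0 | Screened, μ = 0.5 | Screened, μ = 1 |
|---|---|---|---|---|
| 1.5 | about 20% | 2% | 3% | 6% |
| 2 | about 33% | 3% | 6% | 14% |
| 3 | about 62% | 6% | 18% | 44% |
| 4.7 | about 94% | 9% | 47% | 89% |

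**Step 4: equal average recovery, different slopes.** Replacing d·z·m by d·(z − μ)·m makes the factor's effects cancel at the average PA change. The pass rate is then 9 to 11% at every μ. For d = 3 to 4.7 the interaction is found in about 5 to 10% of runs, against 62 to 94% when always fitted.

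**Step 5: other settings.** A separate simulation set the outcome SD at 5.4, the standardised interaction at 0.3 to 0.5 and the marginal association at zero. A continuous factor passed the screen in 13 to 17% of runs. At n = 120 the interaction was found in 9 to 17% of runs with the screen and 92 to 100% without. A larger sample does not open the gate for such a factor.

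**The case against.** Four points can fairly be made for the plan.

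1. **The factors are framed as confounders.** Hypothesis 2 and the description of the measures say so, and the comparison of unadjusted with adjusted models would address that. This stands, and it narrows the point. A reader might infer that the screen shuts off the whole of Objective 2. The protocol does not support that, because the confounding question is still answered. But the section plans interactions, and Objective 2 and the abstract speak of effects on the relationship, so confounding does not exhaust the aim.

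2. **The unconditional adjustment list permits another reading.** If it fixes the model, occupation, FABQ and GHQ12 are already included and their interactions can be tested. This is a possible reading, but the later entry rule contradicts it. The two sentences need reconciling.

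3. **The screen is often passed when PA rises on average.** A reader might infer that modifiers will almost never be tested. That is too strong: at a mean change of 1 SD and d = 3 to 4.7, the pass rate is about 70 to 95%. The protocol states no mean ΔRT3, and zero is the worst case. For d = 1.5 to 2, however, the pass rate at 1 SD is only about 29 to 42%. Where effects cancel around the mean, it stays near 10%.

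4. **The large slope differences flatter the unscreened test.** The design target of 4 points between the upper quartile and the rest is about 2.4 points per SD if ΔRT3 is normal: the two group means are 1.27 and −0.42 SD, and 4/1.69 = 2.4. Differences of 3 to 4.7 exceed that whole effect. This stands: for moderate interactions, removing the screen recovers little power. It does yield an estimate with an interval, which the screened plan withholds.

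A reader might also infer that an untested interaction will be reported as no effect. The protocol does not say how such a result would be reported, so this is a risk to guard against and not a stated intention.

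**Conclusion.** The point holds in limited form. The screening rule is written into the protocol article, so this is not a detail left to a fuller document. Under the screening reading, a marginal test governs which modifiers are examined, and a modifier with no marginal association reaches the interaction test about 10% of the time (13 to 17% if continuous).

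The size of the loss depends on quantities the protocol does not give: the slope difference, the mean ΔRT3, and whether the factor's effects cancel around that mean. It runs from about 5 percentage points (d = 4.7, mean change 1 SD) to about 85 (d = 4.7, mean change zero). For slope differences of 1.5 to 2, low power at n of about 65 limits the analysis with or without the screen. The point concerns a secondary question and does not touch the primary association of ΔRT3 with ΔRMDQ.

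**What to change.** Four changes to the Analyses wording:

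1. State whether the adjusted model contains the fixed list or only the factors that pass p<0.10, and remove the conflict.
2. Name a short list of baseline modifiers tied to Objective 2, for example manual versus sedentary work, FABQ and GHQ12. All are already collected.
3. Fit each ΔRT3-by-factor term, with both main effects, in the adjusted model whatever the factor's univariate p-value. Report the ΔRT3 slopes by level of the factor, with confidence intervals, as secondary and exploratory.
4. State that power for moderate interactions is low at n of about 65 (about 20 to 35% for assumed slope differences of 1.5 to 2 points per SD), and that a non-significant or untested interaction is not evidence of no effect modification.

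The cost is wording, with no new data, visits or participants. The downside is a few named exploratory tests, with the multiplicity they bring, in place of a number set by the data.

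### The Analyses section leaves open whether the listed confounders are forced into the adjusted model or must pass a univariate p < 0.10 screen; if the screen governs, the ΔRT3 coefficient can carry residual confounding.

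*Protocol article*

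**What the plan says.** All the model-building text is in the Analyses section of the protocol article. The exposure of interest is "the main predictor variable, change in RT3 VM counts/hour/week (ΔRT3) from baseline to 3 months", and the outcome is change in RMDQ over the same period.

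On adjustment, the section says: "Adjusted analyses will include the following variables, shown to be putatively associated with both PA and functional recovery in LBP". The list that follows is "age, gender, occupation, baseline pain level (pain questionnaire), functional status (baseline RMDQ) and baseline measurements of depression, anxiety, emotional distress and fear avoidance", the last group measured by GHQ12 and FABQ.

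It then plans a univariate analysis of each explanatory variable against RMDQ change and adds: "We will include factors in the model which in univariate analyses have a *p*-value < 0.10". The significant variables are to be combined and re-examined, together with their interactions with activity change. For those left in the final model, "an examination of their significance (p < 0.05) will be undertaken to evaluate their contribution to the final model".

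Under Hypotheses, psychosocial and occupational factors are said to "act as confounders in the relationship between activity change and the course of LBP over a 1 year period". The Research protocol and timetable section likewise says that occupational and psychosocial data are collected as potential confounders.

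**The concern.** The section gives two descriptions of the adjusted model. One fixes its content from prior knowledge; the other lets the data decide, by a p-value. They give the same model only if every listed variable passes the screen. Nothing says that the list is a candidate pool, that any variable is forced in, or which model is the main adjusted analysis. Two analysts could follow the text and report different ΔRT3 coefficients.

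The screen also does not match the purpose of adjustment. A confounder matters through its links with both exposure and outcome, and the screen looks only at the outcome. In a sample of this size it may drop variables that the protocol itself regards as confounders. In an observational study, the credibility of the adjusted ΔRT3 association depends on how well those variables are controlled.

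**Working it through.** **Sample size at which the screen operates.** The Sample size section gives 65 evaluable participants (SD 5.4, difference 4 points; "The sample size is calculated for 80% power at a two-sided type I error rate of 0.05"). The formula is N = (1 + 1/k)(1 + k)[SD(1.960 + 0.842)/difference]², with k the group ratio. The squared bracket is 14.30. The stated upper-quartile split (k = 3) gives 5.333 × 14.30 = 76.3; k = 2 gives 4.5 × 14.30 = 64.4. So 65 matches a 2:1 split, not the stated 1:3. That is a separate matter, and this point does not depend on it. Recruiting 120 with 40–50% loss leaves 60 to 72, so N = 65 is used below and N = 72 as a check.

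**Chance that a covariate fails the screen.** Let r be its true correlation with RMDQ change. By Fisher's z, P(pass) = Φ(m − 1.645) + Φ(−m − 1.645), with m = atanh(r)·√(N − 3). For r = 0.20 and N = 65, m = 0.2027 × 7.874 = 1.596, so P(pass) = 0.481.

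| r (assumed) | dropped, N = 65 | dropped, N = 72 |
|---|---|---|
| 0.10 | 80% | 79% |
| 0.15 | 67% | 65% |
| 0.20 | 52% | 48% |
| 0.25 | 36% | 32% |
| 0.30 | 21% | 18% |

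These chances do not depend on the covariate's correlation with ΔRT3.

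**Consequence for ΔRT3.** With standardised, independent confounders, the bias with no adjustment is Σ aⱼgⱼ, where aⱼ links confounder j to ΔRT3 and gⱼ links it to the outcome. Eight confounders at 0.20/0.20 give 8 × 0.04 = 0.32; the simulated value is also 0.32. Screening removes part of this. The rows below were simulated at N = 65 with a true ΔRT3 effect of zero and nominal 5% tests. All correlations are assumptions.

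| Confounders (link to ΔRT3 / to outcome) | Screened: bias (SD) | Screened: type I error |
|---|---|---|
| Six, same direction, 0.20 / 0.20 | 0.08 | 9–10% |
| Six, same direction, 0.25 / 0.20 | between 0.08 and 0.14 | about 13% |
| Six, same direction, 0.30 / 0.20 | 0.14 | about 17% |
| Six, same direction, 0.10 / 0.20 | 0.04 | 5.8% |
| Four positive, two negative, 0.20 or 0.30 | 0.03–0.05 | 5.8–6.7% |
| Three positive, three negative, 0.20 or 0.30 | about 0 | 4.8–5.2% |
| Two of six linked to ΔRT3, 0.20 | 0.02 | 5.4% |
| Eight, same direction, 0.20 / 0.20 | 0.11 | 15.2% |
| Eight, same direction, 0.15 / 0.15 | 0.07 | 9.3% |
| Eight, same direction, 0.10 / 0.10 | 0.04 | 5.6% |
| Eight, no link to ΔRT3, 0 / 0.20 | 0 | 5.2% |

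The full list gave bias near zero and type I error of 4.5–5.4% where it was run. For eight confounders at 0.20/0.20, interval coverage was 85% with screening and about 95% with the full list.

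**Two further checks.** At N = 500 the screen left no bias in the 0.20/0.20 case (type I error 4.8%), so the problem comes from the small sample. A masked confounder can also be lost: with a true ΔRT3 effect of 0.3, a link of −0.5 to ΔRT3 and 0.2 to the outcome, its marginal correlation with the outcome is 0.2 − 0.3 × 0.5 = 0.05. It was dropped 87% of the time, with bias −0.08.

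**Cost of the full list.** The SD of the estimate was 0.135 against 0.120 (eight confounders, 0.20/0.20), and 0.173 against 0.132 (six, 0.30/0.20; 0.173/0.132 = 1.31). Root mean squared error in the latter was 0.173 against 0.191.

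**The case against.** The paragraph can be read as one staged procedure: name candidates, screen them, combine the survivors. On that reading the text is loosely worded, not contradictory. This is fair, and a reader who infers a flat contradiction goes further than the wording allows. But the promise to include the list is unqualified, and the staged reading is the one under which the screen can drop stated confounders.

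A reader might also infer that the rule does bias ΔRT3 and inflates type I error to 9–17%. The document does not support that. Those figures need all confounders to push the same way. At 0.30, six of them would explain 6 × 0.09 = 54% of the variance in ΔRT3, and nothing in the protocol suggests this. With mixed signs or weak links, error stays at about 5–7%. Variables with r of 0.3 or more would mostly be kept.

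Nor should the p < 0.05 step be read as a second round of elimination. The text says significance is examined to judge contribution; it does not state removal.

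Finally, the objectives speak of prediction, for which model building is more usual, and unadjusted results will be shown beside adjusted ones. Both mitigate only in part, because the protocol calls these variables confounders and promises an adjusted ΔRT3 association.

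**Conclusion.** The point stands in a limited form. The main adjusted model is not uniquely defined. If the p < 0.10 rule governs, covariates of modest strength (r about 0.2 with RMDQ change) are dropped about half the time at 60 to 72 evaluable participants, so the ΔRT3 coefficient can carry residual confounding. The drop rates follow from the sample size once r is assumed. The consequence does not: its size and sign depend on confounder strengths and directions that the document does not give. The honest range for type I error is about 5% to about 17%, against about 5% for the full list, and there is no bias at all if the covariates are unrelated to ΔRT3. The protocol's own premise is that they are related. This is a stated rule that needs correcting, not detail left to a fuller plan.

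**What to change.** State that the main adjusted model for ΔRT3 contains the full listed set without univariate screening: age, gender, occupation, baseline pain, baseline RMDQ, GHQ12 and FABQ. Enter occupation in a small number of categories, such as the manual/sedentary item already collected, because a detailed occupational coding would use up degrees of freedom. Keep the univariate results, the screened model and the interactions with activity change, labelled as descriptive or exploratory.

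No new data are needed. With single scores and two occupation categories, the model has seven covariates plus ΔRT3, so eight slopes (nine if one covariate needs two terms), which is feasible at 60 to 72 participants. The price is precision: a standard error roughly 10% wider than the screened model's, and up to about 30% if the confounders are strongly related to ΔRT3. The narrower standard error of the screened model is not a gain where it comes with bias.
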